### Enrollment Criteria

#### Inclusion Criteria

The inclusion criteria include being a child from the HDSS site, being younger than 14 days with a parent or guardian or at least 1 person in the household, having a working mobile phone connection, and parent or guardian providing consent to participate in the study.

#### Exclusion Criteria

The exclusion criteria include a child from outside the HDSS area or if the family plans to stay in the catchment area for less than 20 weeks.

### Sampling Strategy and Randomization

The sampling strategy adapted for both sites are as follows (Figure 4).

### Karachi Site

The data for live births and population of each site in Karachi will be obtained from HDSS team. Data will be scrutinized and divided according to 4 sites in the study, with each site consisting of 5 arms (5 clusters). Administrative structures will be assigned to each intervention through stratified (ie, site) randomization.

### Matiari Site

As Matiari site has not been stratified into clusters according to HDSS, we randomly allocated 30 clusters per arm. The catchment area of 4 LHWs will be considered as 1 cluster. Each intervention arm will then be randomly allocated to 24 administrative structures (clusters; see Figure 5).

**Figure 4 figure4:**
[figure not shown]
Cluster Randomization.

**Figure 5 figure5:**
[figure not shown]
Sampling strategy for Karachi and Matiari. For 10% effect size, sampling strategy cluster size=15.

### Recruitment

For Karachi, birth data of the clusters will be shared by central HDSS team on weekly basis and at Matiari the LHWs will inform births to the study team daily according to the study clusters. The study staff will approach families who have an infant younger than 2 weeks in each cluster.

Staff will explain the study objectives to the parents or caregivers. If the parent or caretaker is interested in the study, the infant will be evaluated for enrollment. One child per household will be selected. In a household, where there is more than 1 child (younger than 14 days), a random selection will be made by a program designed in the mobile phone device. After meeting the eligibility criteria, informed consent will be obtained, and the infant will be enrolled in the study and a baseline survey will be conducted.

### Follow-Up Process

A second survey will be conducted at 20 weeks of child’s age (end of follow-up) to identify vaccination coverage according to the schedule, to be confirmed by physical examination of EPI card (see Figure 6).

**Figure 6 figure6:**
[figure not shown]
Participant flow diagram. HDSS: health demographic surveillance systems; SMS: short message service.

### Study Intervention

#### Intervention Group

The intervention arms in addition to the standard counseling will include receiving personalized 1-way or 2- way (interactive) automated SMS or 1-way or 2-way (IVR) automated phone call messages regarding vaccination. In personalized 1-way messages and automated calls, parents will receive educational or reminder or proactive messages related to RI once a week till the child turns 20 weeks. SMS and automated phone calls will contain the same information content and interactive features, only the delivery method will differ. In the interactive arms, in addition to personalized weekly educational or reminder or proactive message, parents will have the option to reply to messages or calls and receive more information related to immunization through SMS text messages or calls (see Figure 7 and Table 4 and Multimedia Appendices 1 and 2). The study timeline has been provided in Table 5.

#### Control Group

The control group will receive 1 time standard verbal counseling at the time of initial visit for on-time EPI vaccines at 6, 10, and 14 weeks of age as recommended by EPI, government of Pakistan.

**Figure 7 figure7:**
[figure not shown]
Details of study arm explained.

**Table 4 table4:** Detail on the personalized weekly short message service and automated calls from enrollment to 20 weeks of life.

Intervention arm	Weekly automated SMS^a^ text message and automated calls from enrollment till 20 weeks of life
Arm 1 (intervention)	Parents or caregivers will receive 1-way educational or reminder or proactive SMS messages related to routine immunization once a week till 20 weeks of age
Arm 2 (intervention)	Parents or caregivers will receive 2-way (interactive) educational or reminder or proactive SMS messages related to routine immunization once a week till 20 weeks of age—parents will have the option to reply and receive more information related to immunization through SMS text messages
Arm 3 (intervention)	Parents or caregivers will receive 1-way educational or reminder or proactive automated phone call related to routine immunization once a week till 20 weeks of age
Arm 4 (intervention)	Parents or caregivers will receive 2-way (interactive) educational or reminder or proactive automated phone call related to routine immunization once a week till 20 weeks of age—parents will have the option to reply and receive more information related to immunization through phone call
Arm 5 (control)	One time counseling at the baseline survey

^a^SMS: short message service.

**Table 5 table5:** Study timeline.

Steps	2018						2019			
	Jan/Feb	Mar/Apr	May/Jun	Jul/Aug	Sep/Oct	Nov/Dec	Jan/Feb	Mar/Apr	May/Jun	Jul
Protocol development	X^a^	—^b^	—	—	—	—	—	—	—	—
Ethical review submission	X	—	—	—	—	—	—	—	—	—
Standard operating procedures	X	—	—	—	—	—	—	—	—	—
Training and implementation of field team	X	—	—	—	—	—	—	—	—	—
Qualitative interviews	X	X	X	—	—	—	—	—	—	X
Trial recruitment	—	—	—	X	X	X	X	—	—	—
Trial follow-up	—	—	—	—	—	X	X	X	X	—
Data entry cleaning and analysis	—	—	—	X	X	X	X	X	X	—
Report and scientific paper writing	—	—	—	—	—	—	—	—	X	X
Thesis completion	—	—	—	—	—	—	—	—	X	X
Additional—baseline, analyses	—	—	—	—	—	—	—	—	X	X

^a^Applicable.

^b^Not applicable.

### Study End Interview

Interviews will be conducted after the trial, with a purposive sample of a subpopulation included in the RCT representing all study arms. From these structured in-depth interviews, we expect to further explore participants’ experience of the different study arms having different levels of coverage. We will also assess the factors related to SMS text messages and automated calls associated with vaccination uptake. Sample size will be guided by saturation of the information.

### Statistical Analysis

Analyses will be conducted according to the intention-to-treat principle. When the information cannot be gathered, the vaccine status of the child will be *failure* (conservative approach). Missing the vaccine EPI card to verify vaccine status at home will lead to a deeper investigation in the family and also the vaccine clinic. From previous experience, we expect this process to be successful in identifying the outcome of over 95% (95/100) of the children who remain in the study at 20 weeks. Families that have left the study for any reason (moving, withdrawal, child death) will be interviewed (if possible) and the information gathered used for the outcome classification. If the information is not clear or incomplete, the child’s status regarding vaccination will be *failure*.

The main analyses will be comparing our 4 study intervention arms against the control, and with each other. For the purposes of our study, we will compare each of the 4 interventions with each other and with the control arm. For example, 1-way versus 2 SMS, reminder versus educational SMS, 1-way reminders SMS versus control, 1-way educational SMS versus control, 2-way reminders SMS versus control, 2-way educational SMS versus control, 2-way education versus 1-way reminder, and 2-way reminder versus 1-way educational.

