#### Sample Size Calculations

Assumptions used for calculating sample size are as follows: increase in coverage rate from 30% to 40%, having a power of 80% with an alpha error at .05. The sample size per arm would be 615 per arm or 3075 for all 5 arms. Adding a 10% dropout will make it 677 per arm or 3385 recruitment for all 5 study arms. The ICC is taken as .05, with an estimate of 15 NB per cluster (see Table 3).

**Table 2 table2:** Cluster randomized clinical trial.

Study arm	Automated SMS^a^ text and phone calls			
	1-way SMS text	2-way SMS text	1-way phone calls	2-way phone calls
1	X^b^	—^c^	—	—
2	—	—	X	—
3	—	X	—	—
4	—	—	—	X
5	—	—	—	—

^a^SMS: short message service.

^b^Applicable.

^c^Not applicable.

**Table 3 table3:** Sample size calculation. Having a difference of 10% and the sample size given (ie, 1230 is 2 groups, 1:1) in our study, we have 5 groups (615x5)+10% dropout=3385.

Serial #	Interclass correlation	Range of cluster size					
		Cluster size of 15		Cluster size of 20		Cluster size of 30	
		Clusters, n	Total birth required, n	Clusters, n	Total birth required, n	Clusters, n	Total birth required, n
1	0.01	54	810	44	880	32	960
2	0.05	82	1230	70	1400	58	1740
3	0.09	108	1620	98	1960	86	2580
4	0.1	114	1710	104	2080	94	2820
5	0.13	134	2010	124	2480	114	3420
6	0.15	148	2220	138	2760	128	3840
7	0.2	180	2700	172	3440	162	4860
8	0.21	188	2820	178	3560	168	5040
9	0.25	214	3210	206	4120	196	5880
10	0.3	248	3720	238	4760	230	6900
11	0.35	280	4200	272	5440	264	7920
12	0.37	294	4410	286	5720	278	8340
13	0.4	314	4710	306	6120	300	9000
14	0.45	346	5190	340	6800	334	10,020
15	0.5	380	5700	374	7480	368	11,040

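### Scoring unknown vaccination status as failure is not conservative for a difference between arms, and the dropout allowance does not match that rule

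*Protocol article*

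**What the plan says.** All references are to the protocol article.

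- **Rule for unknown status** (Statistical Analysis): "When the information cannot be gathered, the vaccine status of the child will be *failure* (conservative approach". A missing immunization card triggers inquiry with the family and the vaccine clinic, and status is expected to be found for more than 95% of children who remain at 20 weeks.
- **Leavers** (same section): "Families that have left the study for any reason (moving, withdrawal, child death) will be interviewed (if possible"), with the answers used to classify the outcome. Unclear or incomplete information again means failure.
- **Target of the analysis** (Analysis of Quantitative Data): the difference in vaccination status, by intention to treat, with a Bonferroni correction. Statistical Analysis compares each intervention arm with control and the intervention arms with each other.
- **Planning** (Sample Size Calculations): "increase in coverage rate from 30% to 40%, having a power of 80% with an alpha error at .05"; "The ICC is taken as .05, with an estimate of 15 NB per cluster"; "The sample size per arm would be 615 per arm or 3075 for all 5 arms"; then "Adding a 10% dropout will make it 677 per arm or 3385 recruitment for all 5 study arms".

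**The concern.** A rule that counts every unknown as unvaccinated is a lower bound for coverage in a single arm. It is not a bound for a difference. If control has more unknowns, control coverage is pushed down further and the intervention looks better. If the intervention arm has more, a real effect is hidden. When SMS is compared with calls, or 1-way with 2-way, neither arm is the one that caution would favour.

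Unequal loss is possible here. Intervention families are contacted weekly to 20 weeks, controls are counselled once (Table 4), and the trial is not blinded. The reassurance in Limitations or Mitigations concerns vaccine completion, not whether completion can be established.

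The sample size has a related mismatch. Its dropout step makes sense if dropouts leave the analysis, but under the failure rule those who stay unresolved remain in it and shrink the difference that the trial was sized to detect.

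**Working it through.** **Inputs.** From Sample Size Calculations: 30% against 40%, power 80%, alpha 0.05 (taken as two-sided, which reproduces the plan's figure), ICC 0.05, 15 newborns per cluster, 10% dropout. From Statistical Analysis: at most 5% unknown among children who remain. Loss by arm is not given and is assumed below. Being unknown is taken as unrelated to true vaccination status.

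**Step 1: the plan's own figure.**

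- Per arm without clustering: [1.96·√(2·0.35·0.65) + 0.842·√(0.30·0.70 + 0.40·0.60)]² / 0.10² = (1.3221 + 0.5646)² / 0.01 = 356.
- Design effect: 1 + (15 − 1)·0.05 = 1.70, and 356 × 1.70 = 605.2.
- Whole clusters: 605.2 / 15 = 40.3, so 41 clusters and 41 × 15 = 615 per arm. Two arms give 82 clusters and 1230, as in Table 3 ("1230 is 2 groups, 1:1").
- Dropout: 615 × 1.10 = 676.5, so 677 per arm and 3385 in five arms.

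The plan's arithmetic is reproduced.

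**Step 2: what the dropout step assumes.** Removing 10% of 677 leaves 609. At 30% against 40% the power is then 80.3%, so the allowance works if dropouts are removed.

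**Step 3: equal unknown share L under the failure rule.** All 677 are analysed (677 / 1.70 = 398 effective), and the rates become 0.30(1 − L) and 0.40(1 − L). Power = Φ[(d − 1.96·SE0) / SE1], where d is the difference, SE0 uses the pooled rate and SE1 the separate rates. For L = 10%: d = 0.09, SE0 = 0.0329, SE1 = 0.0328, so Φ(0.778) = 78.2%.

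| Unknown share L | Observed rates | Power |
|---|---|---|
| 5% | 28.5% vs 38.0% | 81.3% |
| 7% | 27.9% vs 37.2% | 80.1% |
| 10% | 27.0% vs 36.0% | 78.2% |
| 14.5% | 25.7% vs 34.2% | 75.1% |

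The last row is an upper bound: every planned dropout unresolved plus the full 5% of those who remain, 1 − 0.90 × 0.95 = 0.145.

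**Step 4: unequal unknown shares (assumed).** Observed difference = p_I(1 − L_I) − p_C(1 − L_C), for intervention I and control C, with the same 398 effective children per arm.

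| True rates (control, intervention) | Unknown (control, intervention) | Observed rates | Difference | Rejection at 0.05 | Rejection at 0.0125 |
|---|---|---|---|---|---|
| 30%, 30% | 15%, 5% | 25.5%, 28.5% | +3.0 points | 15.9% | 6.1% |
| 30%, 30% | 12%, 8% | 26.4%, 27.6% | +1.2 points | 6.7% | 1.9% |
| 30%, 40% | 5%, 15% | 28.5%, 34.0% | +5.5 points | 39% (power) | not computed |

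The level 0.0125 is 0.05 / 4, for four comparisons with control. The article does not state the Bonferroni divisor. In the first two rows the rejection rate exceeds its nominal level in both columns.

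**The case against.** The strongest reply has several parts.

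- **Tracing.** The plan works to keep unknowns few: card checks, family and clinic inquiry, interviews of leavers, and exclusion of families not planning to stay 20 weeks. Only children who remain unknown dilute the difference. This stands. A reader might infer that the stated 80% power is simply not achieved, but the documents do not support that: power stays at 80% up to about 7% unknown. If the planning rates of 30% and 40% already count unknowns as failures, there is no dilution at all; the article does not say.
- **Unequal loss is conjecture.** The weekly contact is automated, and the 20-week survey is described without distinction by arm. This stands as to size: nothing in the article supports 15% against 5%, and the Bonferroni correction lowers the absolute error rates. It does not rescue the word conservative, because the direction of bias depends on which arm loses more.
- **677 or 684.** One might fault 615 × 1.10 and prefer 615 / 0.90 = 684. This has no consequence, since 609 analysed children still exceed the unrounded 605.2.
- **Recall.** A reader might infer that undocumented recall from leavers counts as success. The article does not say so. It says that the interview information will be used, without naming the evidence required, while Follow-Up Process requires card examination at 20 weeks.
- **The rule itself.** Missing as failure is a defensible pre-specified rule for a coverage endpoint. Multiple imputation assumes data missing at random and needs a decision about children who died. There is therefore no compelling case for making imputation primary.

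**Conclusion.** The point holds in two limited parts.

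First, the justification is wrong for the comparison that the trial makes. Failure scoring biases toward the arm with less missing data, so it can create or hide an effect, and it is not conservative between active arms. How large the bias would be is unknown. The step 4 figures rest on assumed imbalances, a design effect of 1.7 and missingness unrelated to true status. A reader might take them as the trial's expected error rate; they show only how sensitive the result is.

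Second, the dropout allowance and the analysis rule do not agree. The cost is modest: about 78% power instead of 80% if all of the planned 10% stay unresolved, and 75% at the upper bound. These powers use an unadjusted 0.05, as the plan's own calculation does, and clusters of 15. If the 677 sit in the same 41 clusters (about 16.5 each), power at 10% unknown is 76.4%.

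The first part matters more. Both can be corrected in the analysis plan.

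**What to change.** 1. Remove the word conservative. Say that the rule gives a lower bound for coverage within an arm and can bias a difference either way.
2. Keep missing as failure for the main analysis if wished, but report the number and share of unknown status by arm.
3. Pre-specify two sensitivity analyses that must support any claimed effect: multiple imputation that respects clustering and includes arm, site and baseline survey variables, with a stated handling of deaths; and a tipping-point analysis that varies the assumed coverage among unknowns separately by arm.
4. State that a dose counts for leavers on the same card or clinic-record evidence as for children who remain.
5. Restate power under the failure rule, and say whether the planning rates of 30% and 40% already count unknowns as failures.

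The cost is wording, some extra programming and a slightly less favourable stated power. The article reports enrolment complete in January 2019 with exit surveys still under way. Recruitment is unaffected; item 4 bears on how the remaining exit data are collected or coded.

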**Objective:**

The primary objective of this study is to evaluate whether automated mobile phone–based personalized messages (SMS or automated call) can improve RI uptake at 6, 10, and 14 weeks of age per the expanded program immunization schedule, compared with a usual care control group. Secondary objectives include assessing the effects of different types of automated SMS text or calls on RI coverage at 20 weeks of age.

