### Study Objectives

#### Primary

Our first objective is to evaluate whether personalized automated SMS text messages, 1-way versus 2-way, can improve on-time visits at 6, 10, and 14 weeks of age for RI as compared with standard care. Our second objective is to evaluate whether personalized automated calls, 1-way versus 2-way, can improve on-time visits at 6, 10, and 14 weeks of age for RI as compared with standard care. Finally, our third objective is to compare the efficacy of automated SMS text messages versus automated calls on increasing vaccination uptake.

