### Outcomes

#### Primary

Primary outcomes include: (1) to see a 10% increase in RI through personalized automated mobile phone–based communication (SMS or automated call) at 6, 10, and 14 weeks of age according to the EPI schedule versus standard care; (2) to see a 10% increase in RI within 1 week of the original timeline at 6, 10, and 14 weeks versus standard care; (3) to compare coverage rates of personalized 1-way versus 2-way SMS text messages on improvement in RI at 20 weeks of age; (4) to compare coverage rates of personalized 1-way versus 2-way automated calls on improvement in RI at 20 weeks of age; and (5) to compare coverage rates of personalized SMS text messages and automated calls on improvement in RI at 20 weeks of age. 

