### Analysis of Quantitative Data

Analyses will be conducted according to the intention-to-treat principle, and the Bonferroni correction will be used to control for multiple testing. The primary outcome is to assess difference in vaccination status. Chi-square test will first be used to compare the groups’ percentage. Multivariable logistic regression analyses will be conducted to adjust for confounders. As our randomization unit is cluster-based rather than individual-based, generalized linear mixed effects models or generalized estimating equations models will be employed to account for within-cluster correlation, and hierarchal models will be used. The statistical model for the primary and secondary analyses will be developed as explanatory variables. As secondary analyses of the primary outcome, time-to-immunization curves will be constructed using the Kaplan-Meier method and Cox regression for multivariate analysis.

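### Primary outcome 1 asks whether messaging by SMS or call beats standard care, but the main analyses go arm by arm, with no combined contrast and no rule for reading four arm results as one answer

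*Protocol article*

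**What the plan says.** The Abstract (Objective) states one primary question: "whether automated mobile phone–based personalized messages (SMS or automated call) can improve RI uptake at 6, 10, and 14 weeks of age", compared with usual care. Outcomes, Primary, lists first "to see a 10% increase in RI through personalized automated mobile phone–based communication (SMS or automated call") against standard care. Both treat messaging as a class.

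Statistical Analysis describes the main analyses as follows: "The main analyses will be comparing our 4 study intervention arms against the control, and with each other". The next sentence makes this specific: "we will compare each of the 4 interventions with each other and with the control arm". The examples that follow are contrasts of single arms or of message types, such as "1-way reminders SMS versus control, 1-way educational SMS versus control, 2-way reminders SMS versus control, 2-way educational SMS versus control". None combines the SMS and call arms.

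Analysis of Quantitative Data adds that "the Bonferroni correction will be used to control for multiple testing", without saying how many tests share the .05. It also plans mixed models or GEE to allow for clustering.

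Study Objectives, Primary, words the matter differently. It takes SMS and calls in turn, each against standard care; the SMS part reads "evaluate whether personalized automated SMS text messages, 1-way versus 2-way, can improve on-time visits at 6, 10, and 14 weeks of age".

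**The concern.** Four separate arm-versus-control results do not by themselves answer a question about messaging as a class. Three readings are open: outcome 1 is met if any arm is significant, only if all are, or if the arms taken together differ from control. These readings can disagree, and the protocol chooses none of them. The choice could then be made after the results are known, in a trial whose arms are not blinded.

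Even when every arm works equally well, sampling error alone will often make some arms significant and others not. A report built on such a pattern could present chance as a difference between message types. It would also lack an overall estimate of the effect that outcome 1 is about.

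**Working it through.** **Inputs.** From Sample Size Calculations and Table 3: 30% against 40%, 80% power, alpha .05, ICC .05, 15 newborns per cluster, 615 per arm. Assumed: two-sided tests, and a Bonferroni family of 1, 4 or 10 tests. Four is the arm-versus-control tests alone. Ten is all pairs of five arms (5 × 4 / 2). The message-type examples would enlarge the family further if they were tested.

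**The plan's own figure.**
- n = [1.960 × √(2 × .35 × .65) + .842 × √(.21 + .24)]² / .10² = 356 per arm.
- Design effect = 1 + (15 − 1) × .05 = 1.70.
- 356 × 1.70 = 605.2, rounded up to 41 clusters of 15 = 615. This agrees with the protocol. The calculation is for one 1:1 comparison at an uncorrected .05.

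**One arm against control.**
- Effective n = 615 / 1.70 = 361.8.
- SE = √[(.24 + .21) / 361.8] = .0353, so z = .10 / .0353 = 2.84.
- Power is about 81% at .05, 63% at .05/4 and 51% at .05/10.

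**Four arms together, all truly at 40%.** The tests share one control arm, so they are correlated (.21 / .45 = .47). Simulating the five arm proportions by normal approximation gives:

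| Arm-level alpha | No arm significant | Mixed (1 to 3) | All four |
|---|---|---|---|
| .05 | 3% | 40% | 57% |
| .05/4 | 11% | 57% | 32% |
| .05/10 | 19% | 60% | 21% |

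**Combined contrast, each arm weighted 1/4.**
- SE = √[.24 / (4 × 361.8) + .21 / 361.8] = .0273, so z = 3.66.
- Power is about 95% as a single test at .05, but about 79% at .05/11.

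**Ways of answering outcome 1, simulated.** The first column is any arm significant under Bonferroni over the 10 pairs. The other two use Holm over 11 tests (the 10 pairs plus the combined contrast).

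| True rates (control 30%) | Any arm, Bonferroni | Combined contrast alone, Holm | Combined or any arm, Holm |
|---|---|---|---|
| All four 40% | 81% | 79% | 84% |
| Two arms 40%, two 30% | 68% | 21% | 70% |

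With all four arms at 37%, the last rule has 49% power, against 46% for any arm under Bonferroni. Holm also raises the power of a single arm test from 51% to 53% with all arms at 40%. Using a pooled instead of an unpooled variance in the tests shifts the figures in this table by up to about 3 points and does not change the ranking.

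**The case against.** **The combined effect is only one reading of the question.** The body objectives separate SMS from calls, the sample size is for one pairwise comparison, and the Study Hypothesis singles out 2-way calls as possibly preferred. All this suits arm-level tests. The point stands to this extent: the protocol frames its primary question in two ways, and arm-level tests must stay. It does not remove the class-level question in the abstract and in outcome 1.

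**The contrast list is not exhaustive.** It opens as a set of examples, this is a journal article, and an analysis plan may say more. Taken alone, the general sentence on four arms against control could even be read as pooled. But the sentence after it specifies each intervention separately and does not leave the matter open. At best the text is ambiguous on its first primary outcome.

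**Any significant arm is already a valid answer under Bonferroni.** This is correct and limits the point. A reader might infer that a pooled test is the proper sole answer to outcome 1 and is more powerful at the adjusted level. The plan's own figures do not support that: 79% against 81% when all arms work, and 21% against 68% when two do. With pooling as the sole answer and the arm tests ungated, about 48% of trials in the two-arm case would show a significant arm beside a non-significant answer to outcome 1.

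**The .05/10 level is not in the protocol.** This is also correct, hence the range. Low single-arm power partly reflects a sample size set at an uncorrected .05. Mixed results remain common (40%) with no correction at all.

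**Conclusion.** The concern holds as a gap between the first primary outcome and the stated main analyses. With identical true effects in all four arms, a mixed set of results is expected in about 40% to 60% of trials, depending on the unstated Bonferroni family. No arm is significant in about 3% to 19%. The protocol does not say how either pattern answers outcome 1.

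These figures assume 615 analysed per arm, ICC .05, clusters of 15, 30% against 40% in every arm, two-sided tests and a normal approximation. The gap in the text does not depend on them.

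The value of a combined contrast is a defined overall estimate, with a modest gain in power when it is joined to the arm tests under Holm. It is not a replacement for those tests.

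**What to change.** In Statistical Analysis and Analysis of Quantitative Data:

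1. Add the equally weighted average of the four message arms against control as one planned contrast in the mixed model or GEE, and report it with its confidence interval as the effect estimate for outcome 1.
2. Define the multiplicity family as this contrast plus the 10 pairwise contrasts (11 tests), and use Holm instead of single-step Bonferroni.
3. State that outcome 1 is met if the combined contrast or any arm-versus-control contrast is significant in favour of messaging after Holm. Either result means that at least one form of messaging works, and Holm keeps the family-wise error at .05.

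The cost is a few sentences and one more contrast from a model already planned, with no extra children. The 11th test lowers the first threshold from .0050 to .0045, which Holm offsets in the scenarios examined. The remaining drawback is that the pooled estimate is diluted if only some arms work, so it should be shown beside the four arm-level estimates.
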